## Abstract

**Clinical trial registration:**

https://clinicaltrials.gov/, identifier: NCT05646641.

## 1. Introduction

Described in the mid-twentieth century, fibromyalgia is considered a chronic rheumatological disease (1–3) and is included in the International Classification of Diseases (ICD) since 1994. The symptoms usually associated with fibromyalgia are generalized muscle pain, fatigue, sleeping problems, anxiety, depression, headaches, balance impairments, and memory and concentration changes (4, 5). Nevertheless, the diagnosis of fibromyalgia is based on the American College of Rheumatology and criteria are primarily composed of the widespread pain index and the symptom severity scale (6). It is known that the prevalence of fibromyalgia affects around 7% of the world population (7), and it seems to be age and sex-related and varied among countries (8, 9). Indeed, fibromyalgia tended to affect mainly women in any age group, but with more emphasis when above 50 years old (7, 9). This way, it is largely seen as an actual health issue that should be further understood regarding the diagnosis and the efficacy of different strategies that can be used to improve the health and quality of life of people affected.

Fibromyalgia has been associated with alterations in the central and peripheral nervous system that can cause hypersensitivity and allodynia (10, 11). The autonomic nervous system is influenced, modifying the rates of inflammatory mediators (12). As fibromyalgia especially affects somatic tissues, the musculoskeletal system may be the most affected, presenting muscle stiffness, pain, and fatigue (6, 13). Considering these effects, the interest in physical exercise as a co-adjuvant in the treatment and improvement of the quality of life of people with fibromyalgia has grown (14). Considering the benefits of exercise in increasing muscle strength (15), improving balance (16), reducing pain (17), quality of life (18), inflammatory markers (19, 20), among other symptoms and (21), this practice has become well established in the literature. Many studies have shown positive effects of aerobic, strength, resistance and mixed exercises on physical function, fatigue, pain, and muscle strength (4, 14, 22, 23). The effects of isolated practices and specific modalities such as Pilates, Yoga, among others, are currently being sought in the literature (14, 24–27).

It is known that neuromuscular alterations caused by fibromyalgia can cause a risk of disability, as well as an increased risk of falls and injuries (28–30). For this reason, among the different training programs that were assessed, muscle strength training may be essential in combating or even preventing the onset of such issues. However, there is still weak evidence and some studies have focused on the effects of strength training on this population. Indeed, there are still some gaps in the literature regarding the training type and other variables, such as intensity and duration of practice (14, 31–33). Furthermore, the pandemic period in recent years increased the moments of social isolation and mobility restriction, perhaps contributing to accentuating the few exercise habits in this population. At the same time, this created an opportunity to develop and investigate new interventions that are suitable for this new scenario, allowing a safe and viable treatment alternative for this population (e.g., online practice). Most studies with exercise in patients with fibromyalgia are carried out face-to-face. Therefore, this randomized controlled trial protocol aims to structure a study protocol to verify the effects of strength training without external material that will be applied online over a short period (8 weeks), on balance, neuromuscular performance, and symptomatology of fibromyalgia. It is expected that the protocol can be used as a basis and/or an initial protocol for future interventions to clarify and assist the effects of fibromyalgia.

## 2. Materials and methods

### 2.1. Study design

The present study protocol refers to a single-blind, randomized controlled trial, developed according to Standard Protocol Items: Recommendations for Interventional Trials (SPIRIT) (34). The volunteers will be allocated randomly to the intervention group that will receive the exercise program or the control group. A staff member not involved in the study will be responsible for the randomization based on a computer-generated random number. The intervention program will last 12 weeks, consisting of 8 weeks of strength training plus 4 weeks of no training for the intervention group. The 1-month period will serve to evaluate how long the effects of the training will still be present after the training has ceased. The flow chart of the study design is represented in Figure 1.

**Figure 1 F1:**
[figure not shown]
Flow diagram of the study.

### 2.2. Participants

The project will be publicized to find volunteers for the research. For this action, strategies such as flyers, web advertisements, clinical and health professional referrals, email disclosures, and contact from the fibromyalgia associations database will be used for participant recruitment.

After this initial recruitment, participants of both genders with a medical diagnosis of fibromyalgia according to the American College of Rheumatology criteria aged ≥18 years will be eligible to be included in the study. As exclusion criteria, it would be defined as severe comorbidity or any other type of condition that negatively influences participation in the training program; cognitive disorders; heart problems; surgeries or fractures in the last 6 months; regular practice of physical exercises in the least 3 months before the program. Will be discontinued from the study participants that: 1. change medication or dosage during the program; 2. start a regular practice of physical exercises in parallel to the training program; 3. If the participant request. Before the beginning of the program, the participants will be carefully informed about the research, and informed consent must be given before the beginning of the training program. The present research project was approved by the Ethics Committee of the University of Beira Interior, Portugal (CE-UBI-Pj-2021-017).

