### 2.9. Sample size calculation

The G-power software was used to detect a moderate effect size (partial eta squared of 0.09) in the intra/inter-group comparison. Considering an alpha value of 5%, the total number of participants should be 24 so that the power of the results is 90%. Considering a 20% of dropout risk, a minimum of 30 participants will be recruited (15 for each group).

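### Section 2.2 discontinues anyone whose medication changes during the program, but no entry criterion screens for medication still being adjusted, as one does for exercise

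*Protocol article*

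**What the plan says.** Section 2.2 admits "participants of both genders with a medical diagnosis of fibromyalgia according to the American College of Rheumatology criteria aged ≥18 years will be eligible". It then lists the exclusions. Two are tied to a period before entry: "surgeries or fractures in the last 6 months; regular practice of physical exercises in the least 3 months before the program". The others are cognitive disorders, heart problems and a general item, "severe comorbidity or any other type of condition that negatively influences participation in the training program". None refers to medication.

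The discontinuation rules follow directly: "Will be discontinued from the study participants that: 1. change medication or dosage during the program". The second rule covers people who take up regular exercise alongside the program, and the third covers the participant's own request.

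Section 2.1 gives the program as 12 weeks, 8 of training and 4 without. Section 2.4 places randomisation after the eligibility check, with 1:1 allocation. Section 2.7.2 asks controls to keep to their usual medical treatment; it does not require that this treatment was stable beforehand. Section 2.9 sets 24 participants for 90% power and then allows for loss: "Considering a 20% of dropout risk, a minimum of 30 participants will be recruited", 15 in each group.

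**The concern.** Two behaviours end participation under section 2.2: starting regular exercise and changing medication. The plan screens for the first before entry and monitors it afterwards. It only monitors the second. If a medication change matters enough to take someone out of the study, it would be consistent to ask about it before that person is randomised.

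Two things are at stake. First, a volunteer found at screening to be in mid-adjustment costs no randomised data, whereas the same person removed after allocation does. Second, someone whose last adjustment fell just before baseline may stay in with pain, fatigue, sleep, mood or FIQ-P scores that are still moving for reasons unrelated to the arm. With 15 per group, a few such people add variability and could be split unevenly by chance.

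**Working it through.** **1. The two rules side by side (section 2.2).**

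| Factor | Entry criterion | Rule during the program |
|---|---|---|
| Regular exercise | Excluded if practised in the preceding 3 months | Discontinued if started |
| Medication or dosage | None | Discontinued if changed |
| Surgery or fracture | Excluded if within 6 months | None |

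The general exclusion concerns conditions that hinder taking part in training. A recent dose change is not such a condition on its face, so it does not fill the gap.

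**2. Path of one participant.** A volunteer with the diagnosis, aged 18 or over, part-way through a medication adjustment, meets every written criterion. Section 2.4 then randomises that person. If the next adjustment falls within the program, the first discontinuation rule applies.

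**3. The plan's own sample size.** Inputs from section 2.9: partial eta squared 0.09, alpha 0.05, power 90%, 20% dropout. Assumed, because the article does not state them: three measurement times (m), correlation 0.5 between them, sphericity, and the group-by-time interaction test.

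- f² = 0.09 / (1 − 0.09) = 0.0989.
- Noncentrality = f² × N × m / (1 − correlation) = 0.0989 × 24 × 3 / 0.5 = 14.24, with 2 and 44 degrees of freedom.
- Power = 0.914 at N = 24, the smallest even total that reaches 0.90. The stated 24 reproduces.
- 24 / (1 − 0.20) = 30. The stated 30 reproduces.

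**4. The allowance.** 30 − 24 = 6 participants. Section 2.9 names no cause of dropout and excludes none, so these 6 must cover every loss, medication changes included.

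**5. How much of it this gap might use.** The documents give neither the share of entrants in mid-adjustment (s) nor the share of those who change again during the program (r). Removals = 30 × s × r. With assumed values only:

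| s | r = 25% | r = 50% | r = 100% |
|---|---|---|---|
| 10% | 0.75 | 1.5 | 3 |
| 20% | 1.5 | 3 | 6 |
| 30% | 2.25 | 4.5 | 9 |

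Only the most extreme cell exceeds 6 by itself. The range runs from under 1 to 9, so the answer depends on inputs that the documents do not supply. I do not carry it through to completers or power: that would need to know how far these removals are already within the planned 20%, which section 2.9 does not say.

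**The case against.** **There is no contradiction.** A rule for events during the program is compatible with having no window before it. This stands: the point concerns two adjacent rules that fit together poorly. It is a design choice that could be improved.

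**The loss may already be budgeted.** A reader might infer that medication removals come on top of the planned 20%. Section 2.9 does not support that, because its dropout risk is general. Nor do the documents show that everyone in mid-adjustment changes again, or that recently adjusted people are the likeliest to change. An entry window would also not stop a person who was stable at entry from changing later, so how much loss it prevents is unknown.

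**Loss and noise cannot both be charged to the same people.** Someone removed does not add variability among those who finish. This stands, and the two effects are alternatives for any one participant.

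**No bias follows from the entry rule.** A reader might infer a distorted treatment effect. Instability before baseline precedes a 1:1 random allocation, so it produces noise and possible chance imbalance. Bias could arise if removal during the program depends on arm, but that belongs to the discontinuation rule.

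**The bigger issue is the removal itself.** If people who change medication were kept and analysed, the loss part of this point would disappear and only the noise argument would remain. This also stands.

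A further limit is that the rule speaks of the program. The period after randomisation largely coincides with it but need not be identical.

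**Conclusion.** The point holds in a limited form. Section 2.2 controls exercise before and during the program but medication only during it, so the plan can enrol and randomise people whom its own rule then removes. That follows from the text and needs no assumed rate.

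The size is unknown and probably modest. What is fixed is the all-cause margin of 6 participants. How much of it goes to people who could have been identified at screening depends on two rates that the documents do not give. No completer count, power loss or variance increase should be attached to this point.

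It is an optional, inexpensive improvement. The absence of a medication item from the baseline data in section 2.6 is not part of the finding, since an article may leave that detail to the full protocol.

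**What to change.** Reconcile the entry criteria in section 2.2 with the first discontinuation rule. Add an exclusion for recent start of, or change in, fibromyalgia-related medication or dosage, and check it before randomisation under section 2.4. The investigators should set the window; nothing in the documents fixes its length. The criterion governs only who enters and when, and alters no one's treatment.

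The cost is one line of eligibility text and one screening question, plus a slightly narrower population or a short wait for some volunteers. The change does not settle how participants removed after randomisation are followed and analysed, which needs its own answer.

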### 2.4. Randomization

After evaluation of the inclusion and exclusion criteria, the participants eligible to participate in the study will be randomly separated into two groups: the control group (CG): which will have no activities performed; the experimental group (EG): which will follow the strength exercises protocol.

The randomization of the participants will be performed by an individual not directly related to the study. To avoid selection bias, random numbers will be generated by computer; the distribution will be made from a website: www.randomization.com. For the statistical analysis, the researcher in charge will receive the data without identifying the participants to obtain the results in a blinded manner. A randomization with a 1:1 computer-generated will be made for the group allocation.

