#### 2.6.2. Visual analog scale

For the evaluation of the other symptoms related to fibromyalgia, for the present study, the Visual Analog Scale (VAS) (37) was chosen for the analysis of pain intensity, anxiety level, fatigue level, mood, and quality of sleep. This scale consists of a 100-millimeter horizontal line with boundaries at each end, in which the final rating is measured from the distance from the initial end to the mark by the participant. In this way, each millimeter will be equivalent to one unit. The scoring range will be from 0 to 100, in which the higher the value, the greater the intensity. Scores between 0 and 30 mm will be classified as “mild pain”; between 40 and 70 mm as “moderate pain” and between 80 and 100 mm as “severe pain.”

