#### 2.7.2. Control group

Participants included in the control group in a randomized manner will be instructed to maintain their usual medical treatment and daily routines during the experimental intervention period, which did not include structured exercise. After the end of the protocol, the patients were re-evaluated and invited to receive the training program. After the end of the protocol and the re-evaluation, control group participants will be given the opportunity to perform the training program.

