### 2.8. Retention and adherence

To maintain adherence, individualized attention will be prioritized during the session and especially the care regarding pain control of everyone at the beginning, during and at the end of each session. In case of absence, the participant will be contacted for information regarding his/her health status or other reasons. In case of withdrawal from the program, the reason will be investigated to be identified at the end of the study.

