### 2.10. Statistical analysis

SPSS software will be used. To verify normality either the Shapiro-Wilk test (n < 30) will be used, and the equality of variances will be assessed by the Levene test. If the data, follow a normal distribution inter-group and intra-group differences will be calculated by repeated measures analysis of variance (ANOVA). If the data do not follow a normal distribution, the Kruskal-Wallis test will be calculated for between-group differences and the Friedman test for intra-group differences. To calculate the effect size, Cohen's test (intra-group comparison) will be used, and the between-group variance (partial eta squared) will be estimated. To verify the reliability of the tests and their measurements, the coefficient of variation and the intraclass correlation coefficient will be calculated. Finally, to evaluate the relationships between variables, Pearson's correlation coefficient will be calculated. The significance level will be set at 0.05.

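### Section 2.2 takes participants out of the study after randomisation if they change medication or start exercising, so later outcome data may be lost selectively

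*Protocol article*

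**What the plan says.** Section 2.2 lists three grounds for discontinuation. The first is "Will be discontinued from the study participants that: 1. change medication or dosage during the program". The second reads "2. start a regular practice of physical exercises in parallel to the training program". The third is the participant's own request, which is ordinary withdrawal and not at issue here.

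Section 2.4 fixes the order of events: "After evaluation of the inclusion and exclusion criteria, the participants eligible to participate in the study will be randomly separated into two groups". Section 2.1 gives the length of the program: "The intervention program will last 12 weeks, consisting of 8 weeks of strength training plus 4 weeks of no training for the intervention group". Both arms are assessed at baseline, in the week after training ends, and again after the four weeks off training (section 2.5).

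Controls "will be instructed to maintain their usual medical treatment and daily routines during the experimental intervention period" (section 2.7.2). On losses, section 2.8 says "In case of withdrawal from the program, the reason will be investigated to be identified at the end of the study". Section 2.9 allows 20% for dropout, and section 2.10 plans repeated measures ANOVA, with Kruskal-Wallis and Friedman tests if the data are not normal. The article does not say that people discontinued under section 2.2 are still assessed.

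**The concern.** The first two grounds are events after randomisation that end a person's part in the study. The first is plausibly tied to outcome. The visual analogue scale "was chosen for the analysis of pain intensity, anxiety level, fatigue level, mood, and quality of sleep", and a change in any of these symptoms is a plausible reason for a person with fibromyalgia to change a drug or a dose. The criterion covers any change, so a reduction after improvement counts as much as an increase after worsening.

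The arms also differ in what could prompt a change, since one trains under supervision twice a week and the other does nothing new. If removal depends on both outcome and arm, those who remain are no longer comparable in the way randomisation made them. Training could look better or worse than it is. With 15 per group, a few selective losses matter.

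**Working it through.** **1. Timing.** Eligibility is checked, then participants are randomised (2.4), then the program runs (2.1). Anything that happens during the program is therefore after randomisation. Someone discontinued during the 8 training weeks misses both later assessments; someone discontinued in the off-training weeks misses the last. Repeated measures ANOVA in its standard form uses only participants with every visit, so either loss removes the person from that analysis.

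**2. The plan's own sample size.** Partial eta squared 0.09 gives f = sqrt(0.09/0.91) = 0.3145. I assume a group-by-time interaction with 2 groups, 3 visits, correlation 0.5 between visits and sphericity; the article states neither of the last two.
- Noncentrality = f² × N × m/(1 − rho) = 0.0989 × 24 × 3/0.5 = 14.24, on 2 and 44 degrees of freedom.
- Power = 91.4% at N = 24, and 24/0.8 = 30.

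The stated 24 and 30 reproduce and are not in dispute. The allowance is 6 people for all losses together. Under the same assumptions, power is 96.5% with 30 analysed, 91.4% with 24, 88.6% with 22, 84.9% with 20 and 80.3% with 18. Spare numbers protect precision. They do nothing about selective loss.

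**3. Illustration of bias.** The documents give no rate of medication change, so these inputs are assumptions: no true effect, normal change scores with SD 1, 15 per arm, 3 removed from one arm and none from the other, and a two-sided 5% t test of 12 against 15.
- The three most extreme of 15 standard normal values have expected values of about 1.74, 1.25 and 0.95, which sum to 3.93. Removing exactly those three shifts the mean of the other 12 by 3.93/12 = 0.328 SD.
- If removal follows a variable with correlation r to the change score, the expected shift is r × 0.328. The false-positive rates below are simulated.

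| r | Shift (SD) | False-positive rate |
|---|---|---|
| 0.3 | 0.10 | about 6% |
| 0.5 | 0.16 | about 7% |
| 0.7 | 0.23 | about 10% |
| 1.0 | 0.33 | about 16% |

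The last row requires that exactly the three worst scores are removed.

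**4. Other removal patterns** (simulated; lower score is better; rates and odds ratios assumed).
- Removal unrelated to outcome: no bias.
- No true effect, and the same outcome-dependent removal in both arms: no bias.
- True effect −0.63 SD (about 2f), removal on worsening with odds ratio 2 to 4 per SD, 10% to 40% of controls removed: the effect among those left shrinks to between −0.61 and −0.49 SD.
- No true effect, 20% to 40% of controls and 10% of trained participants removed on worsening: a false difference of 0.07 to 0.30 SD against training.
- No true effect, controls removed on worsening and trained participants on improvement, 10% to 30% per arm: a false difference of 0.13 to 0.62 SD against training.

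Removing mainly the trained participants who worsen would reverse the sign.

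**The case against.** The rule has a legitimate purpose. Holding medication and other exercise constant limits confounding by co-intervention, and a trial may reasonably want to know the effect of training alone. Section 2.2 ends participation but does not say that data already collected are discarded, and an analysis plan that is not shown may define an as-randomised set. Both points stand, and they limit the claim to outcome data after the event. An analysis set cannot restore assessments that were never made because the person had left the study.

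A reader might also infer more than the documents support:
- **That such changes are common over 12 weeks and use up the 20% allowance.** No rate is given. Section 2.9 does not list the causes behind its 20%, so these discontinuations may already be counted.
- **That controls are the more likely to take up exercise.** Section 2.2 excludes people who already exercise regularly. Section 2.7.2 asks controls to keep their routines and offers them the program afterwards, which weakens the motive.
- **That the exercise criterion works like the medication one.** Its link to outcome is weaker. It is tied to the training program, which lasts 8 weeks, and it is unclear whether it reaches controls at all.
- **That a false-positive rate near 16% is to be expected.** That figure needs removal to be fully determined by outcome, in one arm only.

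**Conclusion.** The point holds in limited form and should be fixed. Section 2.2 states a rule that ends study participation after randomisation, for events of which at least one, a medication change, is plausibly connected with the trial's symptom outcomes and may differ by arm. Followed as written, it loses later outcome data in a way that need not be random.

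The outcome link is an inference, not a statement in the article. The direction of any bias cannot be determined from the documents. With 3 of 15 lost from one arm and a moderate correlation (0.3 to 0.7), the shift is about 0.10 to 0.23 SD and the false-positive rate about 6% to 10%; 0.33 SD and 16% is the ceiling of that scenario. Larger artefacts need opposite removal patterns in the two arms. It would go too far to say that the result is certain not to be an as-randomised effect, because the rates are unknown and the handling of data collected before discontinuation is not described.

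**What to change.** In section 2.2, separate discontinuation from outcome collection and leave every rule on training and medication as it is:
- Record the medication change or new exercise with its date. Section 2.8 already plans to establish reasons for withdrawal, so part of this exists.
- Keep the scheduled assessments for these participants for as long as they consent.
- Analyse them in the arm to which they were randomised, for example with a mixed model that uses all available visits.
- Add a sensitivity analysis that leaves out data after the change.
- State whether the exercise criterion applies to controls, and over which weeks.

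The cost is a short amendment and the effort of assessing a few more people. No extra recruitment is needed, and keeping people in helps power (96.5% with 30 analysed against 91.4% with 24, under the assumptions above). The downside is that the main estimate then includes the effect of co-interventions. The sensitivity analysis addresses the question without them, with the selection problem in plain view. The change has to come before follow-up is lost, because missed assessments cannot be recovered.
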